## Abstract

**Background:**

Obesity is a major problem in the United States, particularly among socio-economically disadvantaged Latino and Black children. Effective interventions that can be disseminated to large numbers of at-risk children and their families are needed. The goals of the Early Childhood Obesity Prevention Program (ECHO) are to examine the 12-month efficacy of a primary obesity prevention program targeting the first year of life that is delivered by home visitors and that engages mothers as agents of change to modify their own behavior and their infant’s behavior through education and skill-building around nutrition, physical activity, and wellness, and then “echoes” her training with linkages to neighborhood programs and resources.

**Methods/Design:**

Six family centers located in low-income neighborhoods in Hartford, CT were randomized into control and intervention neighborhoods. Fifty-seven mothers were recruited either prenatally or shortly after delivery into the Nurturing Families Network home visitation program; 27 lived in a control neighborhood and received the standard home visitation program and 30 lived in an intervention neighborhood and received both the standard home visitation program and the ECHO intervention. The intervention increases maternal skills in goal-setting, stimulus control and problem-solving, engages family members to support changes, links mothers to neighborhood resources and is embedded in the standard home visitation program. ECHO targets include breastfeeding, solids, juice and sugar-sweetened beverages, routines for sleep and responding to infant cues, television/screen time, and maternal diet and physical activity. We hypothesize that infants in ECHO will have been breastfed longer and exclusively, will have delayed introduction of solids and juice, have longer sleep duration, decreased television/screen time and a lower weight for length *z*-score at 12 months, and their mothers will have greater fruit and vegetable consumption and higher levels of physical activity.

**Discussion:**

ECHO will provide important information about whether an enhanced behavior change curriculum integrated into an existing home visitation program, focused on the mother as the agent of change and linked to neighborhood resources is effective in changing energy balance behaviors in the infant and in the mother. If effective, the intervention could be widely disseminated to prevent obesity in young children.

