**Fig. 1 Fig1:**
[figure not shown]
Ecological model of obesity prevention program

Home visitors can support behavior change effectiveness and can reach high-risk pregnant women and mothers during this early and critical period in a culturally responsive way [14–16]. National home visitation programs provide health and psychosocial-related services to at-risk pregnant women and mothers of infants and toddlers [17, 18]. Home visitors have been used to improve self-management of diabetes and asthma and a few trials of home visitation for the prevention of obesity are currently on-going [19–22].

The Nurturing Families Network (NFN) is a nationally recognized, evidence-based home visitation program with credentialed educators, and in Connecticut, is a program of the Children’s Trust Fund. The NFN Home Visitation Program uses two evidence-based curricula (*Parents as Teachers-Born to Learn* (PAT) and *Partners for a Healthy Baby* (Partners)) and a culturally diverse workforce [23, 24]. Both curricula achieve positive parenting and child outcomes, prevent child abuse, and enhance child development [25, 26]. The curricula provide some education on breastfeeding (2–3 h), introduction of solids, and infant routines, but the content is primarily education-focused and mothers are not taught behavioral skills to implement recommended behaviors. The effect of the NFN Home Visitation Program on maternal obesogenic behaviors and its role in obesity prevention in young children are not known.

Obesity prevention programs that begin before habits have become established and that use home visitors and a developmental perspective to address environmental and community contextual issues in a culturally responsive way may be successful in preventing obesity in young children. These interventions, however, need to be delivered early in life since rapid weight gain in the first 6 months of life predicts future obesity in children, independent of birth weight [27–31].

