Potential goals for interventions in children in the first year of life include increasing breastfeeding, reducing sugar-sweetened beverage (SSB)/juice consumption, delaying the introduction of solids, limiting television/screen time, establishing infant routines around sleep, and recognizing infant cues to hunger and satiety. Breastfeeding decreases initial weight gain and is one strategy for reducing childhood overweight [32], although recent studies [33–37] have not found an obeso-protective effect. Breast milk, however, is the best nourishment for infants, and is a low-cost, readily available nutrient [38]. The American Academy of Pediatrics recommends no solids and no juice in the first 6 months of life but, in the United States, by 6 months of age, 50 % of infants consume sugar-sweetened beverages/juice daily [39], and 65 % consume solids, usually cereals [40]. Early SSB consumption has been associated with obesity [41] while delaying the introduction of solids to 6 months of age and not mixing cereal in bottles reduces mean weight for length [42]. Television viewing is obesogenic [43] and the American Academy of Pediatrics recommends no television/screen time for children less than 2 years and no television in the bedroom [44]. Helping parents to establish sleep routines and to recognize cues for hunger and satiety are obeso-protective while infant sleeping duration less than 11 h per day is associated with rapid weight gain by 6 months [45, 46].

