We hypothesized that at 6 and 12 months, as compared to NFN infants, NFN+ infants would have been breastfed longer and more often exclusively, would drink less sugar-sweetened beverages/juice, would have begun to ingest solids at an older age, and would sleep more hours/day, have more established sleep/wake routines, greater soothability and have fewer hours of television viewing/day. Secondary hypotheses of the study included that at 6 and 12 months, as compared to NFN families, NFN+ families would purchase, cook and serve more fruits and vegetables, demonstrate greater utilization of BFF Centers and community resources, and NFN+ infants would be less likely to have a weight for length greater than the 85^th^ percentile. The study protocol was approved by the Institutional Review Board at Connecticut Children’s Medical Center, was sponsored by the Hartford Childhood Wellness Alliance, and was funded by the National Institutes of Health (NICHD R21 HD073966-A01).

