#### Secondary outcome variables

Maternal diet and behavior are being assessed using self- report on maternal fruits, vegetables, and beverage consumption [67]. Mothers are asked how many days per week they eat breakfast, lunch, dinner, and snacks and how many days per week they eat at fast-food or other restaurants. Information about the food and beverages in the home is obtained. The Paffenbarger Health Fitness Assessment is being used to assess maternal activity [68]. Infant weight and length with calculation of the weight for length *z*-score are determined by medical record review at birth, 6 and 12 months.

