## Discussion

New models and interventions to prevent childhood obesity and reverse the staggering increases in obesity prevalence over the past 40 years are needed. Interventions need to not only be successful but to also be capable of wide dissemination and implementation at reasonable cost.

The Early Childhood Obesity Prevention Program (ECHO) is a randomized controlled trial testing the efficacy of the early establishment of healthy behaviors in preventing childhood obesity in mothers of Latino and Black children from a low-income, urban community. It is an innovative, ecologically- and culturally-based intervention to obesity prevention. The intervention builds upon an existing home visitation program by incorporating maternal education with skill-building (goa-setting, problem-solving, self-monitoring, and stimulus control). The intervention then uses these core behavioral strategies to target 4 specific areas of behavior change (breastfeeding, delayed introduction of solids, delayed consumption of fruit juice, and infant routines including limiting television/screen time, recognizing cues for hunger and satiety and sleep duration) that mothers are open to change. The intervention has been designed to be incorporated into ongoing home visits which will enhance opportunities for wide dissemination. The intervention is also grounded in Behavior Theory and the Ecological Model of Childhood Obesity to activate mothers to implement new behaviors in the home. The intervention links mothers to community programs and resources, supports maternal changes, and provides feedback on achievement of specific goals determined by the mother within a culturally responsive framework. It also addresses concerns in Latina and Black mothers about weight as a sign of health, breastfeeding, television as an educational tool, and outdoor safety. The study is innovative in its focus on newborns, the use of mothers as agents of change, and the utilization of an existing home visitation program to enhance mother-infant outcomes. The intervention also sets the stage for lasting and endurable change by taking into account the child’s environmental and social milieu and connecting families to neighborhood programs and resources to support behavior change.

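### The article presents the trial as a test of obesity prevention, but its success criterion and primary outcomes are behaviors, and the secondary weight comparison is too imprecise to support an obesity claim

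*Protocol article*

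**What the plan says.** The main Discussion calls ECHO a "randomized controlled trial testing the efficacy of the early establishment of healthy behaviors in preventing childhood obesity". In the Abstract's Discussion, the question is whether the enhanced curriculum "is effective in changing energy balance behaviors in the infant and in the mother". The next sentence reads: "If effective, the intervention could be widely disseminated to prevent obesity in young children".

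The primary outcomes (Primary outcome variables; Evaluation plan; Statistical analysis plan for primary outcomes) are breastfeeding, sugar-sweetened beverages and juice, solids, sleep, soothability and television. The exact list varies a little between sections, but none includes a growth measure. Feeding, sleep and soothability come from maternal questionnaires. In the RE-AIM framework, Effectiveness means maternal behaviors at 6 months and short-term attrition.

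Growth is planned as a secondary matter:

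- The Abstract's Methods/Design hypothesizes a lower weight-for-length z-score at 12 months.
- Overview and hypotheses adds, among the secondary hypotheses at 6 and 12 months, that "NFN+ infants would be less likely to have a weight for length greater than" the 85th percentile.
- Under Secondary outcome variables, infant weight and length "are determined by medical record review at birth, 6 and 12 months".
- The Evaluation plan examines z-scores at 12 months under Maintenance.
- The analysis plan for secondary outcomes introduces a z-score comparison but specifies a chi-square test on weight categories.

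The Background justifies intervening early because "rapid weight gain in the first 6 months of life predicts future obesity in children, independent of birth weight".

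**The concern.** The criterion for success is behavioral, and the conclusion drawn from success is about obesity. The step between them needs either a growth result precise enough to carry it or a secure link from each behavior to obesity. The article claims neither. For breastfeeding, the first outcome listed, its Background reports that recent studies "have not found an obeso-protective effect". It also warns that education and maternal behavior change may fall short of preventing obesity where food access and neighborhood safety are lacking.

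At stake is how a positive result would be read. A funder or home-visiting program deciding on dissemination could take a change in reported feeding or screen time as evidence on obesity, while the weight data could neither confirm nor exclude an effect.

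**Working it through.** **The plan's own figure.** The only power statement (Sample size, power calculation) concerns a fall of about 0.3 in the proportion given SSB/juice and/or solids before 6 months. It is a behavioral figure and states no baseline rate, so its 80% cannot be reproduced uniquely. No power is stated for any weight outcome, so the weight figures below contradict no stated number. They show what the weight comparison can bear.

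**Inputs.**
- Infants analyzed: 60 × (1 − 0.20) = 48, or 24 per arm (Sample size, power calculation).
- Two-sided 0.05: the article gives 0.05, and two-sided is assumed.
- Control proportion above the 85th percentile: not given; 15% to 35% assumed.
- Effect: that proportion halved (assumed).
- Clustering ignored. The six centers, three per arm, would be expected to lower these figures. No intracluster correlation is given, so the loss is not sized.

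**Proportion above the 85th percentile.** Power is the sum, over all pairs (a, b), of Bin(a; 24, p) × Bin(b; 24, p/2) for those pairs where the test rejects.

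| Control vs intervention | Chi-square | Fisher |
|---|---|---|
| 15% vs 7.5% | 12.7% | 6.4% |
| 20% vs 10% | 16.7% | 9.7% |
| 25% vs 12.5% | 20.5% | 12.8% |
| 30% vs 15% | 24.5% | 16.1% |
| 35% vs 17.5% | 28.7% | 19.7% |

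Normal-approximation check for 30% vs 15%, with pooled proportion 0.225:
- Null SE = √(2 × 0.225 × 0.775 / 24) = 0.1206.
- Alternative SE = √((0.30 × 0.70 + 0.15 × 0.85) / 24) = 0.1186.
- Power = Φ((0.15 − 1.96 × 0.1206) / 0.1186) = Φ(−0.73) ≈ 23%, in line with the exact 24.5%.

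By the same approximation, 80% power would need 278 infants per arm at 15% vs 7.5%, 199 at 20% vs 10%, and 121 at 30% vs 15%.

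**Mean weight-for-length z-score.** The normal formula gives (1.96 + 0.842) × √(2/24) = 0.81 SD for 80% power. The t-test with 46 degrees of freedom gives 0.83 SD. By the normal formula, power is 10% for a true difference of 0.2 SD, 18% for 0.3 SD and 41% for 0.5 SD. The 95% confidence interval half-width is 2.013 × √(2/24) = 0.58 SD.

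**Numbers that met final eligibility.** With the 23 control and 26 intervention dyads of Table 2, and no later loss, chi-square power is 11% to 27% over the same range, and 0.82 SD is needed for 80% power.

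**The case against.** The best case on the other side is that this is only wording. The Abstract says what *effective* means one sentence before the quoted one, its conclusion is conditional, and the sample size section calls the study an initial efficacy trial limited by budget. No decision rule depends on either Discussion statement. Weight for length also fits much of the Background, which links the timing of solids to it and cites a home-visiting study that reduced it. Early weight gain is offered as a reason for starting early, not as an endpoint.

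Much of this stands, and it rules out three stronger readings that a reader might infer:

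- *That the obesity claim rests on reported behaviors only.* It does not. Record-based weight for length is a pre-specified secondary outcome, hypothesized in the Abstract and in Overview and hypotheses, and compared between arms.
- *That growth data go unanalyzed.* Weight categories and 12-month z-scores are to be examined. The article describes no analysis of weight gain from birth to 6 months, but it condenses a fuller plan and its analytic figure is not shown. That silence does not establish an omission.
- *That longer breastfeeding alone would be counted as obesity prevention.* No passage sets such a rule. The Background reports the null studies openly and gives other reasons for promoting breastfeeding.

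What the objection does not rescue is the main Discussion, where the trial is said to be "testing the efficacy of the early establishment of healthy behaviors in preventing childhood obesity". No qualification there confines that to behaviors. The article's modesty elsewhere is a reason to bring these statements into line with it.

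**Conclusion.** The point holds as a mismatch between claim and design. The trial can test whether targeted behaviors change. At about 24 infants per arm it cannot test obesity prevention unless the effect on weight is very large: chi-square power for a halving is about 13% to 29%, and a mean difference of about 0.83 SD is needed for 80% power. The proportions rest on assumed control rates and an assumed halving. The z-score figure, in SD units, needs neither. Both ignore clustering, so they are probably optimistic.

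The behavioral comparisons are not invalidated. The matter is worth correcting because the affected sentences are the ones a reader deciding on dissemination will use, and because reducing a hypothesized z-score to categories discards information from a sample that has little to spare.

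**What to change.** 1. Reword the Abstract's Discussion and the main Discussion. The trial tests change in infant and maternal behaviors, and *effective* refers to those targeted behaviors. A positive result supports a larger trial with a growth primary outcome and is not by itself evidence of obesity prevention.
2. Base any obesity-related statement on a continuous growth estimate with a 95% confidence interval that allows for neighborhood clustering, in place of the chi-square on categories. Use the weight-for-length z-score already hypothesized. As an added secondary analysis, compare 6-month weight between arms given birth weight, which matches the early-gain marker in the Background. The category comparison can stay as description.

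The cost is two reworded passages, one changed analysis and one extra secondary analysis, all from records already being abstracted. The price is a more modest headline. The growth estimates will still be imprecise: adjusting for birth weight may help somewhat, but three neighborhoods per arm limit what any allowance for clustering can achieve. The interval should be reported as showing what the trial leaves open.

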**Trial Registration:**

ClinicalTrials.gov NCT02052518 January 30, 2014.

## Background

The prevalence of obesity in the United States has tripled in the past 40 years [1] with disproportionately higher rates in low-income children of color [2–4]. Socioeconomic and racial/ethnic disparities in rates of obesity appear during the preschool years [3]. Not surprisingly, children with an elevated body mass index before 5 years of age are at increased risk of becoming obese adults, suggesting a need to intervene early in life [5].

Many childhood obesity prevention efforts have focused on school-age children [6]. There is a small but growing body of literature on obesity prevention in young children [7–9]. These studies in young children suggest that parental involvement and engaging parents as agents of change are keys to early obesity prevention [10, 11]. One recent pilot study educated mothers to recognize infant cues and to delay the introduction of solids [11]. A second study used home visitors and incorporated maternal education into the *Parents as Teachers* program to increase fruit and vegetable consumption; they demonstrated a reduced weight for length and changes in parental behavior [12].

Thus, parental education and maternal behavior change appear to be important components of obesity prevention. They may not, however, be sufficient to prevent obesity if mothers do not have access to, cannot afford, or don’t know how to prepare quality food and/or don’t feel safe in their community. Ecological models of obesity (Fig. 1) recognize the broader contextual influences on individuals including families, neighborhoods, culture and the greater society. Interventions using an ecological model support families to sustain change and, in adults, have been shown to promote greater weight loss [13].

**Fig. 1 Fig1:**
[figure not shown]
Ecological model of obesity prevention program

Home visitors can support behavior change effectiveness and can reach high-risk pregnant women and mothers during this early and critical period in a culturally responsive way [14–16]. National home visitation programs provide health and psychosocial-related services to at-risk pregnant women and mothers of infants and toddlers [17, 18]. Home visitors have been used to improve self-management of diabetes and asthma and a few trials of home visitation for the prevention of obesity are currently on-going [19–22].

The Nurturing Families Network (NFN) is a nationally recognized, evidence-based home visitation program with credentialed educators, and in Connecticut, is a program of the Children’s Trust Fund. The NFN Home Visitation Program uses two evidence-based curricula (*Parents as Teachers-Born to Learn* (PAT) and *Partners for a Healthy Baby* (Partners)) and a culturally diverse workforce [23, 24]. Both curricula achieve positive parenting and child outcomes, prevent child abuse, and enhance child development [25, 26]. The curricula provide some education on breastfeeding (2–3 h), introduction of solids, and infant routines, but the content is primarily education-focused and mothers are not taught behavioral skills to implement recommended behaviors. The effect of the NFN Home Visitation Program on maternal obesogenic behaviors and its role in obesity prevention in young children are not known.

Obesity prevention programs that begin before habits have become established and that use home visitors and a developmental perspective to address environmental and community contextual issues in a culturally responsive way may be successful in preventing obesity in young children. These interventions, however, need to be delivered early in life since rapid weight gain in the first 6 months of life predicts future obesity in children, independent of birth weight [27–31].

Potential goals for interventions in children in the first year of life include increasing breastfeeding, reducing sugar-sweetened beverage (SSB)/juice consumption, delaying the introduction of solids, limiting television/screen time, establishing infant routines around sleep, and recognizing infant cues to hunger and satiety. Breastfeeding decreases initial weight gain and is one strategy for reducing childhood overweight [32], although recent studies [33–37] have not found an obeso-protective effect. Breast milk, however, is the best nourishment for infants, and is a low-cost, readily available nutrient [38]. The American Academy of Pediatrics recommends no solids and no juice in the first 6 months of life but, in the United States, by 6 months of age, 50 % of infants consume sugar-sweetened beverages/juice daily [39], and 65 % consume solids, usually cereals [40]. Early SSB consumption has been associated with obesity [41] while delaying the introduction of solids to 6 months of age and not mixing cereal in bottles reduces mean weight for length [42]. Television viewing is obesogenic [43] and the American Academy of Pediatrics recommends no television/screen time for children less than 2 years and no television in the bedroom [44]. Helping parents to establish sleep routines and to recognize cues for hunger and satiety are obeso-protective while infant sleeping duration less than 11 h per day is associated with rapid weight gain by 6 months [45, 46].

Understanding the context in which obesogenic behaviors occur, helping parents of very young children to establish positive behaviors, and linking families to community resources could prevent the development of obesity in young children. These goals are the foundation of an intervention called the *Early Childhood Obesity Prevention Program (ECHO): Building Healthier Families and Communities.* ECHO is a randomized, controlled trial designed to examine the efficacy at 12 months of a home visitation program that engages mothers as agents of change to modify their own behavior and their infant’s behavior through education and skill building in the areas of nutrition, physical activity, and wellness, and then “echoes” her training with linkages to neighborhood programs (e.g., coupons to purchase fruits and vegetables at grocery stores and farmer’s markets, parenting classes at Family Centers, neighborhood cooking classes). ECHO recruits pregnant women and new mothers who have agreed to participate in NFN’s home visitation program and provides them with an enhanced curriculum that increases maternal skills in goal-setting, problem-solving, and stimulus control to target four specific infant-related behaviors (breastfeeding, SSB/juice consumption, introduction of solids, television/screen time and infant routines and cues around sleep and hunger and satiety) and follows the mother-infant dyad until the infant is 12 months of age. The program also provides education and linkages to community resources to improve the mother’s health, nutrition and physical activity. The study’s focus on newborns and mothers as agents of change adds to the small literature on obesity prevention in this critical developmental window.

